### Recruitment

Participants will be recruited from at least four mental health centers with six locations in the east and west of the Netherlands and will start in September 2018. Possible participants are informed by means of flyers and posters distributed in these centers. In order to include sufficient participants, mental health professionals will play an active role, by informing potentially eligible patients about the study and handing out information folders.

### Intervention

We will adapt the positive psychology intervention *“*This is your life*”* [38, 39] for patients with BD in the euthymic phase aiming to enhance personal recovery and well-being. Originally developed as a self-help book, the intervention is primarily based on the well-being theory of Seligman [40] and Ryff’s theory of psychological well-being [41] and comprises different modules focusing on six key components: positive emotions; discovering and using strengths; optimism and hope; self-compassion; resilience and post-traumatic growth and positive relations. Each module contains psycho-education and a range of different positive psychology exercises, such as the “three good things exercise” [33] or the “best possible self” [42]. All modules include proven strategies for improving well-being. In a recent randomized controlled trial, the intervention as guided self-help with email support revealed moderate to large effects on well-being (*d* = 0.66) and effectively reduced subclinical symptoms of anxiety (*d* = 0.63) and depression (*d* = 0.43) in a non-clinical sample [39].

### Intervention adjustments for euthymic BD patients

Since *“*This is your life*”* was not specifically developed for individuals with BD, we decided to customize the intervention content and delivery to the needs of this target group. The adjusted intervention is called “Living well with bipolar disorder”. We changed the mode of treatment delivery from individual self-help to group meetings (8–10 people per group), including eight sessions of 2 h conducted by a specially trained therapist. This setup is believed to give participants the possibility to share experiences with fellow patients and benefit from the presence of other group members.

Each week, a key positive psychology component will be covered and corresponding exercises will be introduced. Participants are also encouraged to keep training with those exercises at home (for 15–30 min per day). All intervention participants receive the self-help book *“*This is your life*”* [43], since several parts of the modules refer to chapters or exercises in the book. The adapted intervention consists of eight different modules covering different topics, such as positive emotions, positive relationships or personal goals. Homework differs depending on the module, but every week participants are encouraged to keep training with the exercises at home. Experiences with the homework is discussed at the beginning of each next session and possible obstacles or other benefits can be shared with the therapist and other group members. In case the module contains a collective exercise, a short debriefing session will take place immediately after the exercise, to discuss experienced benefits or difficulties. Every module contains a short break of 15 min. Every session is finished by a short conclusion in which the therapist summarizes the session and where uncertainties can be broached and questions can be asked.

In spring 2017, a formative user evaluation of *“*This is your life*”* was carried out to evaluate the original intervention contents. Five individuals with BD read and practiced a selection of the original exercises and rated them on a scale from 1 (*not at all*) to 5 (*extremely*), representing the relevance and usability of the exercises. Results of this group were used to further adapt and tailor the intervention to the needs of individuals with BD by taking into account the ratings of exercises, preferences of the patients and also their critical responses.

For several reasons, we decided to put additional emphasis on fostering self-compassion skills by including two sessions of self-compassion. Research on emotion regulation [44–46] emphasizes the importance of disturbed positive emotion regulation (i.e., how an individual reacts to positive emotions) for the onset, maintenance and illness course of BD [47]. Suppression of positive emotions is heightened among BD patients and predicts depressive and also manic symptoms [48, 49]. Additionally, negative thinking about high moods (e.g. “I will lose control if I get excited”) is also elevated in individuals with BD, compared with nonclinical controls [50–52], individuals with remitted unipolar depression [50, 52] and individuals who have had hypomanic experiences, but no psychological disorder [50] and predicts mood symptoms in BD over the period of 1 month [53] and 6 months [49]. Studies show that self-compassion is positively related with adaptive emotion regulation processes, including acceptance and positive reappraisal and negatively correlated with maladaptive strategies, such as thought suppression and rumination [54–56]. An overview of the intervention contents can be found in Table 1.

**Table 1 Tab1:** Content of “Living well with bipolar disorder” and corresponding example exercises adapted for euthymic BD patients

Module	Contents	Example (home) exercises
1. Introduction & compassion	▪ Participants are welcomed and become familiar with each other ▪ Psychoeducation about personal recovery and compassion ▪ Collective compassion exercise ▪ Homework: Fill in handout about personal goals and optimism	▪ Wish yourself something good: be mindful and identify needs and use your inner voice to repeat your compassionate wish [86]. ▪ Common humanity: Realize that negative feelings and experiences are universal [87, 88].
2. Personal goals & optimism	▪ Based on the handouts, participants talk about personal goals and wishes and specify personal goals in the group ▪ Individually adjusting personal goals ▪ Collective optimism exercise ▪ Reading and discussing letter from an experienced person with BD ▪ Homework: Working on personal goals, writing a letter from the future	▪ Imagine your best possible self: Visualize yourself in a future where everything has turned out in the most optimal way [42, 89]. ▪ Letter from the future: write yourself a letter from a future perspective
3. Positive emotions	▪ Read out letter from the future ▪ Psychoeducation about positive emotions ▪ Collective positive emotions exercises ▪ Homework: Taking a photo of a positive moment or experience, working on personal goals	▪ Three good things: Think about three good things that went well today and savor these moments [90]. ▪ Expressing gratitude: identify what you are grateful for in the context of your illness and share those experiences [91].
4. Coping with fear of relapse	▪ Sharing photos of positive experiences and talking about the photos ▪ Talking about participant’s fears, how fear is experienced and internal barriers ▪ Psychoeducation about fear and (un)healthy emotion regulation strategies ▪ Collective exercises on how to efficiently cope with fear ▪ Homework: Do something you find exciting, perform personal strengths exercise, completing mid-treatment measurement	▪ Learn to tolerate and accept fear as important part of life and learn to regulate positive mood and gain a more open view towards them [43]. ▪ Compassionate coping with inner fear: learn to be compassionate towards yourself, your emotions and your negative experiences [86].
5. Personal strengths	▪ Identifying strengths ▪ Psychoeducation about personal strengths ▪ Personal goals and strengths: which strengths can be used to achieve personal goals? ▪ Homework: Keep training with exercises, record possible benefits and barriers while performing the exercises	▪ Identifying strengths: Describe an activity you enjoy to someone else and he/she names strengths deriving from this activity. ▪ Top 5 strengths: Choose your top 5 strengths that give you energy and pleasure [92, 93].
6. Positive relationships	▪ Participants name skills they gathered in the course of the intervention so far and described one example from the last week ▪ Psychoeducation about positive relationships ▪ Participants describe a relationship they want to reinforce positively ▪ Collective positive relationship exercises ▪ Homework: Keep training with positive relationship exercises	▪ Acts of kindness: Performing unexpected acts of kindness for someone else [94]. ▪ Active-constructive responding: Respond positively to good news shared by someone else. Use active communication skills [95, 96]. ▪ Expressing gratitude [91].
7. Compassion	▪ Psychoeducation about emotional systems and evolutionary background ▪ Collective exercises mindfulness and compassion ▪ Coping with thoughts of inferiority and self-critique ▪ Homework: Writing a response to the letter from the second session, fill in questionnaires for post-measurement	▪ Develop a compassionate inner voice: Write about situation in the past week where you showed self-compassion [86]. ▪ Grandma exercise: Imagine a person you feel comfortable with. Concentrate on how it feels to be together with this person and savor this moment [43].
8. Conclusion	▪ Talking about results of the questionnaires and figuring out which aspects are going well and which should receive some extra attention in the next weeks ▪ Read out response to the letter from the second sessions ▪ Participants thank each other	▪ Not applicable.

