## Method

### Study design

A pragmatic, parallel-group randomized non-blinded multicenter trial is used to investigate the effectiveness of a multicomponent positive psychology intervention to improve well-being and personal recovery in patients with BD. Since the outcome in BD I and BD II disorder may be different, the sample will be stratified accordingly. Patients in the experimental condition receive “Living well with bipolar disorder” in addition to CAU. Participants in the control condition receive CAU only. Both participants in the control and experimental condition receive CAU according to the Dutch multidisciplinary guideline for BD [13], consisting mainly of self-monitoring of mood and supportive group sessions focusing on functional problems, and psychopharmacotherapy. The study duration is 12 months for each individual and includes five measurement points. Immediately prior to the start of the intervention a baseline measurement is completed (T0), 4 weeks after the start of the intervention a mid-treatment measurement takes place (T1) and immediately following the intervention a post measurement will be conducted (T2). In addition, two follow-up measures will be conducted, 6 months (T3) and 12 months after baseline (T4). Figure 1 shows the intended flow of participants (Additional file 1).

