### Study procedure

Initial screening for participation will be performed by therapists working at the treatment centers. To assess symptom severity of possible participants, the Clinical Global Impression Scale – Bipolar (CGI-BP) is used. After possible participants sign the informed consent, the principal investigator contacts the patient and agrees on a time and date to conduct the additional screening. To verify the diagnosis of BD, the MINI international neuropsychiatric interview [37, 57] is used and to assess well-being, participants are asked to complete the Mental Health Continuum – Short Form (MHC-SF) [58]. Eligible participants are then asked to complete the first test battery at baseline. Since the MHC-SF has already been completed for screening reasons before, participants are not asked to complete it again at baseline. Baseline measurements should take approximately 40 min to complete. Afterwards, allocation of participants to the intervention or control group takes place.

The first intervention group will start approximately in fall 2018 and the last group will finish in fall 2019. Four weeks after the intervention begins (T1) and after the intervention has finished (T2), participants in the intervention and control condition are asked to fill out a test battery again. Six (T3) and 12 (T4) months after baseline, participants in the experimental and control group will be asked to complete the follow-up measures. We assume that completing the test battery takes approximately 35 min on average at each measurement point. At T4, participants will be approached for a semi-structured telephone interview with the goal to retrospectively assess relapse into mood episodes in the past 9 months. To perform the interviews, a guideline will be prepared and the interviews will be conducted by student assistants according to a fixed scheme. The trained student assistants are blind to the treatment condition of the participants. One interview will take approximately 30 min.

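### Table 1 sets the T2 questionnaires as homework before the last session and makes their results session material, in the intervention arm only, although the text places T2 after the intervention in both arms

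*Protocol article*

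**What the plan says.** Two parts of the protocol article describe when T2 is taken.

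- **Study design:** "immediately following the intervention a post measurement will be conducted (T2").
- **Study procedure:** "after the intervention has finished (T2), participants in the intervention and control condition are asked to fill out a test battery again".
- **Table 1, module 7, homework:** "Writing a response to the letter from the second session, fill in questionnaires for post-measurement".
- **Table 1, module 8:** "Talking about results of the questionnaires and figuring out which aspects are going well".

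The section on adjusting the intervention describes the programme as "including eight sessions of 2 h conducted by a specially trained therapist", so session 8 belongs to the intervention. The same section says that homework is taken up at the start of the following session, where "possible obstacles or other benefits can be shared with the therapist and other group members".

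The design is given as "A pragmatic, parallel-group randomized non-blinded multicenter trial". Study measures says that nearly all data are self-reported through an online survey. The power calculation rests on well-being at post-intervention. It labels that time point T1, but by the design and procedure sections post-intervention is T2, and I read it so.

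**The concern.** The two descriptions of T2 cannot both be followed. If sites follow Table 1, intervention patients answer before the last session, prompted by their therapist, and the results become material for the next group meeting. Controls receive usual care only, and no matching assignment or discussion is described for them.

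The outcome is self-reported and patients know their arm. A difference in how and for whom the answers are given can therefore shift reported well-being in one arm only. Such a shift is confounded with treatment: neither intention-to-treat analysis nor the linear mixed model can separate it from an effect. A homework prompt could also make T2 completion differ between arms. The Discussion names non-specific factors and attrition as limitations, but not this. The pragmatic argument it gives does not cover it either. Group contact is part of the treatment being tested, whereas the conditions under which the outcome is recorded are not.

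**Working it through.** **1. Timing, side by side.**

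| Place | When T2 is completed | Arm |
|---|---|---|
| Study design | directly after the intervention | both |
| Study procedure | after the intervention has ended | both |
| Table 1, module 7 | as homework between sessions 7 and 8 | intervention |

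Sessions are weekly, so under Table 1 the intervention arm answers up to about one week before the programme ends.

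**2. Which questionnaires module 8 means.** Module 8 speaks only of the questionnaires. The only ones set in the preceding homework are those for the post-measurement. That they are the same is an inference, but a close one.

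**3. The plan's own figure.** Two-sided independent t-test, d = 0.60, alpha 0.05, power 80%: the exact calculation gives 44.59, rounded up to 45 per arm (power 80.4%). With 20% dropout, 90 / 0.8 = 112.5, against 112 in the plan. The sample size reproduces, and this point does not change it.

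**4. Illustration of a reporting shift.** The documents give no size for such a bias. Assume no true effect and an upward shift of b SD in the intervention arm. With n = 45 per arm, the test statistic is noncentral t with 88 degrees of freedom and noncentrality b × √(n/2) = b × √22.5. The rejection probability is the mass beyond the two-sided critical value: 1.987 at alpha 0.05, and 2.550 at alpha 0.0125.

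The second threshold reflects the planned Holm-Bonferroni correction. Well-being is measured at four post-baseline times (T1 to T4), so the first step is 0.05 / 4 = 0.0125. It is the relevant step if T2 has the smallest p-value.

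| Assumed shift b | Noncentrality | Rejection at 0.05 | Rejection at 0.0125 |
|---|---|---|---|
| 0 | 0 | 5% | 1.25% |
| 0.1 SD | 0.474 | 7.6% | 2.3% |
| 0.2 SD | 0.949 | 15.5% | 5.9% |
| 0.3 SD | 1.423 | 29.1% | 13.6% |

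A shift of 0.2 SD would be 0.2 / 0.6, a third of the effect the trial is sized for.

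**5. The opposite direction.** Answering before session 8 leaves that session out of the score. If it carried a full eighth of the effect, d would be 0.60 × 7/8 = 0.525, and power at 45 per arm would fall from 80% to 69% at unadjusted alpha 0.05. This is an upper-end assumption: module 8 is a conclusion and lists no exercises.

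**The case against.** The best defence is that the practical difference is small and its direction uncertain. By the time T2 is completed under Table 1, all seven content modules have been given. Any loss from the missing concluding session pulls toward no difference. The same battery goes to both arms, and one online mode is described. The size and sign of a reporting shift are assumed, and an open trial with self-reported outcomes carries expectation bias anyway. All of this stands, and it limits the size that can be claimed. It removes neither the contradiction nor the arm-specific setting, which comes on top of the ordinary expectation bias and is avoidable.

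Several stronger readings are tempting but not supported:

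- **Confidentiality is breached.** A reader might infer this from the discussion in module 8. The article promises confidential, ID-coded handling, and nothing gives therapists or group members access to the answers. Nor does it say whether scores or general impressions are discussed, or that patients are told of the discussion before they answer.
- **The whole primary endpoint is compromised.** The stated aim covers short- and long-term improvement, the mixed model uses repeated measurements, and T3 and T4 are not set as homework. Only the T2 contrast is affected, though the sample size rests on it.
- **T1 has the same fault.** It is homework of module 4, but this agrees with its timing at four weeks, and module 5 lists no discussion of results.
- **The unadjusted error rates are the trial's error rates.** They ignore the planned Holm-Bonferroni correction, which lowers them as shown.

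**Conclusion.** The point holds for T2. Table 1 contradicts the Study design and Study procedure sections on when T2 is taken. Followed literally, it creates for one arm only a setting in which a self-reported outcome is a therapist's assignment and its results are session material. In a non-blinded trial this can bias the T2 comparison, and the planned analyses cannot remove that bias.

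The timing conflict is certain from the text. The bias is plausible, but its size is unknown. The range of 7.6% to 29.1% (unadjusted), or 2.3% to 13.6% against a nominal 1.25% (first Holm step), rests wholly on an assumed shift of 0.1 to 0.3 SD, no true effect and 45 per arm. The early timing in itself is minor and acts the other way. The link to session 8 rests on reading its questionnaires as the post-measurement set.

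**What to change.** Reconcile Table 1 with the Study design and Study procedure sections before the first group starts:

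1. Remove the T2 questionnaires from the module 7 homework.
2. Send T2 through the online survey after session 8, in the same window and with the same invitation for both arms.
3. State that therapists neither see nor use trial answers.
4. For the module 8 review, use a separate reflection sheet that is not trial data.

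The T1 homework needs no change on this ground.

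The cost is small: revised manual text, a changed survey date and a changed activity in session 8. The last is a real, if minor, alteration of intervention content. The article says that the manual is still to be prepared, so the change can be made there. No additional patients are needed.

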### Control group

Participants in the comparison group will receive CAU for BD as described in the Dutch multi-disciplinary guideline for bipolar disorder [13] which comprises supportive sessions with a psychologist or psychiatric nurse and maintenance pharmacological treatment by a psychiatrist. Most patients receive 2–12 supportive sessions per year. CAU includes many psychoeducational elements that have the following aims: to give patients information about the illness in the context of the patients’ life-history, to learn to identify early warning signals and prodromal symptoms, to develop and implement strategies to cope with prodromal symptoms, and to develop plans for acute crisis and stabilizing one’s mood. For some patients, CAU may additionally include psychotherapeutic treatments such as cognitive behavioral therapy and interpersonal therapy. For all patients, current CAU does not primarily focus on personal recovery in terms of emotional and psychological well-being (i.e. meaning, purpose in life, positive relationships).

### Therapists training and treatment manual

Therapists carrying out the intervention will receive a one-day workshop covering the central ideas of *“*Living well with bipolar disorder*”,* including background, goals and possible exercises of the intervention. A treatment manual will be prepared to guarantee a standardized execution of the intervention. The manual includes explanations on each module and also on corresponding exercises. Short session handouts (1–2 pages) will be developed for patients participating in the intervention, explaining and summarizing the topics of each module and will include affiliated exercises and can be used to further exercise at home.

### Study procedure

Initial screening for participation will be performed by therapists working at the treatment centers. To assess symptom severity of possible participants, the Clinical Global Impression Scale – Bipolar (CGI-BP) is used. After possible participants sign the informed consent, the principal investigator contacts the patient and agrees on a time and date to conduct the additional screening. To verify the diagnosis of BD, the MINI international neuropsychiatric interview [37, 57] is used and to assess well-being, participants are asked to complete the Mental Health Continuum – Short Form (MHC-SF) [58]. Eligible participants are then asked to complete the first test battery at baseline. Since the MHC-SF has already been completed for screening reasons before, participants are not asked to complete it again at baseline. Baseline measurements should take approximately 40 min to complete. Afterwards, allocation of participants to the intervention or control group takes place.

The first intervention group will start approximately in fall 2018 and the last group will finish in fall 2019. Four weeks after the intervention begins (T1) and after the intervention has finished (T2), participants in the intervention and control condition are asked to fill out a test battery again. Six (T3) and 12 (T4) months after baseline, participants in the experimental and control group will be asked to complete the follow-up measures. We assume that completing the test battery takes approximately 35 min on average at each measurement point. At T4, participants will be approached for a semi-structured telephone interview with the goal to retrospectively assess relapse into mood episodes in the past 9 months. To perform the interviews, a guideline will be prepared and the interviews will be conducted by student assistants according to a fixed scheme. The trained student assistants are blind to the treatment condition of the participants. One interview will take approximately 30 min.

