### Study measures

Almost all data being gathered during the trial are self-reported data that will be collected via an online survey program (https://www.qualtrics.com). In addition, one semi-structured telephone interview will be conducted 12 months after baseline to assess relapse. Participants will be asked to report demographical data including gender, age, marital and employment status, ethnicity and education, as well as the information about the past course of BD, at baseline. The primary outcome is well-being and secondary outcomes include personal recovery, social role participation and symptoms of depression, mania and anxiety. Additionally, processes of positive emotions, self-compassion and positive relationships are assessed and economic outcomes are used to calculate the cost-effectivness. An overview of the study measures at the different time points can be found in Table 2*.*

**Table 2 Tab2:** Overview of study parameters and measurement points

Questionnaire	Outcome	Screening	T0	T1	T2	T3	T4
			Pre-test	Mid-treatment^a^	Post-test	Follow-up^b^	Follow-up^c^
CGI-BP^d^	Global illness severity	X					
MINI	Diagnosis BD	X					
MHC-SF	Well-being	X	X	X	X	X	X
QPR	Personal recovery		X		X	X	X
s-SRPQ	Social participation		X		X	X	X
QIDS-SR	Depressive symptoms		X		X	X	X
ASRM	Manic symptoms		X		X	X	X
HADS-A	Anxiety symptoms		X		X	X	X
PANAS	Positive emotions		X	X	X		
SCS-SF	Self-compassion		X	X	X		
SPWB	Positive relationships		X	X	X		
RPA	Dampening of positive affect		X	X	X		
Telephone interviews	Relapse						X
EQ-5D-5 L	Quality of Life		X				X
TiC-P	Costs associated with psychiatric illness		X				X
Socio- demographics	Gender, age, education, marital status, living situation, ethnicity		X				

^a^4 weeks after intervention begin

^b^6 months after baseline

^c^12 months after baseline

^d^clinician reported

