#### Relapse

Semi-structured telephone interviews will be performed with people of both the intervention and control group. Goal of the interviews is to retrospectively illustrate the mood development in the time after the intervention and to capture depressive or manic mood swings with the Life Chart Method [80]. The interviews allow to graphically score severity of mood swings, the time they appeared (i.e., in which month) and which type of mood swings appeared (e.g., rapid cycling). The interview has been applied successfully in a previous study to measure relapse [14].

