#### Statistical analyses

Analyses will be done on both intention to treat (ITT) and per-protocol basis. The primary ITT analyses will be performed using linear mixed modelling (LMM) that adequately deals with missing at random data and the nested structure of repeated-measures data. LMMs with time, treatment and time-by-treatment interactions will be performed to test the effectiveness of the intervention in improving continuous primary and secondary outcomes of well-being, personal recovery, psychopathology, sef-compassion, positive relationships and dampening. Post-hoc independent t-tests with Holm-Bonferroni correction will be performed to test for significant between-group differences at all time-points. Based on estimated marginal means and corresponding standard errors from the LMM models, between-group standardized effect sizes will additionally be expressed as Cohen’s d with 95% confidence intervals (CI). Binary relapse data from the interviews will be analyzed with Kaplan Meyer survival estimates to compare the time to relapse and relapse rates between the intervention and control group. Differences in the proportion of relapsed patients and predictors of relapse will be additionally examined using generalized (binary) LMMs with post-hoc chi-square tests and relative risks (RR) with 95% CI to examine the significance and magnitude of differences at each follow-up point. Moderation and mediation analyses will be conducted to explore possible working mechanisms of the interventions. To calculate the cost-effectiveness of the intervention, quality adjusted life years (QALYs) will be taken into account as primary utility measure. QALYs will be calculated from the EQ-5D-5 L. The incremental cost-utility ratio (ICUR) will be calculated by dividing the difference in costs calculated from the TiC-P by the difference in the QALYs produced by the two groups. The ICUR is expressed as costs per QALY gained.

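### The single relapse interview at month 12 looks back only 9 months, so relapses in the first 3 months after baseline go unrecorded and the relapse comparison does not cover the full randomised follow-up

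*Protocol article*

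**What the plan says.** Four parts of the Protocol article bear on this point.

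- **Timeline.** Study design states: "The study duration is 12 months for each individual and includes five measurement points". Baseline (T0) is placed immediately before the intervention starts, and T4 is 12 months after baseline. Study procedure puts randomisation after the baseline battery: "Afterwards, allocation of participants to the intervention or control group takes place". The Background gives the intervention length as eight weeks.
- **Relapse measurement.** Study measures states that "one semi-structured telephone interview will be conducted 12 months after baseline to assess relapse", and Table 2 marks the interview at T4 only. Study procedure says it is held "with the goal to retrospectively assess relapse into mood episodes in the past 9 months".
- **Scope.** The Relapse section describes the goal differently, as to "retrospectively illustrate the mood development in the time after the intervention", using the Life Chart Method, which places mood swings by month.
- **Analysis.** Statistical analyses plans "Kaplan Meyer survival estimates to compare the time to relapse and relapse rates between the intervention and control group". It adds generalised mixed models and relative risks at each follow-up point. No time origin for the survival curves is given.

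Reducing recurrence in the long term is the fourth aim listed in the Background. The primary outcome is well-being.

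**The concern.** The interview date and the look-back length leave a stretch of follow-up about which nobody is asked. It begins at randomisation, the moment from which a comparison of the randomised groups should run. Three things follow if the plan is carried out as written.

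- A patient who relapses only in months 0 to 3 is recorded as relapse-free.
- A patient who relapses early and again later is given the wrong date of first relapse.
- The analysis cannot be rescued by restricting it to patients still relapse-free at month 3, because the interview does not identify them.

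At stake is the relapse aim, the one outcome collected by interviewers blind to allocation in an otherwise non-blinded trial that relies mostly on self-report. Early relapse may differ between arms, so a comparison that starts at month 3 no longer has the full protection of randomisation. No later analysis plan can recover information that was never requested.

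**Working it through.** The plan gives no derivation for the nine months, so there is no calculation to reproduce. The check is whether nine months fits either start point that the article offers.

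**Inputs from the article**
- Interview at month 12 after baseline (Study measures; Table 2)
- Look-back of 9 months (Study procedure)
- Baseline immediately before the intervention (Study design), with allocation after baseline (Study procedure)
- Intervention of 8 weeks (Background)

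**Step 1: where the window opens.** 12 − 9 = month 3. Uncovered share of follow-up: 3/12 = 25%. At the 6-month follow-up point, 3/6 = 50% of the elapsed time is uncovered.

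**Step 2: what lies in the gap.** One month is 365.25/12/7 = 4.348 weeks, so 8 weeks = 8/4.348 = 1.84 months. The gap holds the whole intervention (1.84 months) plus 3 − 1.84 = 1.16 months after it, and 1.16 × 4.348 = about 5 weeks.

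**Step 3: the look-back each start point would need.**

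| Start of relapse follow-up | Look-back needed at month 12 | Stated |
|---|---|---|
| T0/randomisation | 12 months | 9 months |
| End of the 8-week intervention | 12 − 1.84 = 10.16 months | 9 months |

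Nine months fits neither.

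**Step 4: whether another measure fills the gap.** Table 2 lists the depression and mania self-reports (QIDS-SR, ASRM) at T0, T2, T3 and T4. They are symptom scores at a point in time, and the article does not define relapse from them. Statistical analyses says the relapse data come from the interviews. The gap stays open for relapse.

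**Step 5: how many first relapses could fall in it.** The article gives no expected relapse risk for this trial, so I assume a 12-month risk p, equal in both arms, and a constant hazard. The risk by month 3 is 1 − (1 − p)^(3/12), and the share of first-year first relapses in the gap is that figure divided by p.

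| Assumed p | Risk by month 3 | Share in gap |
|---|---|---|
| 0.20 | 0.054 | 27% |
| 0.30 | 0.085 | 28% |
| 0.40 | 0.120 | 30% |
| 0.50 | 0.159 | 32% |
| 0.60 | 0.205 | 34% |

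Steps 1 to 4 need no assumption beyond the article's own dates. Step 5 is an illustration.

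**The case against.** **Leaving out the treatment period is deliberate.** The Relapse section limits the interview to the time after the intervention, and the aim concerns the long term. Against that scope the shortfall is about 5 weeks, not 3 months. The Randomization section also says groups start once enough participants are randomised. A wait of about 5 weeks between baseline and the first session would put the end of treatment near month 3. This stands in part: the nine months may have been chosen with such a wait in mind. But Study design places baseline immediately before the start, so the article contradicts that reading. A deliberate post-intervention window would still not support a comparison from randomisation.

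**The time origin is not stated.** True, and the interview guideline is still to be prepared. That the curves will not start at randomisation is an inference, but one forced by the missing data on months 0 to 3.

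**A reader might infer that the gap dilutes the treatment effect.** The article does not support this. Take the median times to relapse that the Background quotes from a pilot of a different intervention (18 weeks usual care, 56 weeks treated) and exponential times. The 12-month relative risk is (1 − 2^(−52/56))/(1 − 2^(−52/18)) = 0.475/0.865 = 0.55. Counting only first-ever relapses in weeks 13 to 52 gives 0.326/0.471 = 0.69, which looks like attenuation. That rule drops later episodes in early relapsers, whom the interview would record. Counting any episode in the 39-week window at a constant rate gives (1 − 2^(−39/56))/(1 − 2^(−39/18)) = 0.38/0.78 = 0.49, slightly stronger than 0.55. The direction depends on the counting rule. The exponential model also fits the pilot poorly. At 65 weeks it predicts 92% and 55% relapsed, about 74% overall with equal arms, against the quoted 32 of 67 (48%), although censoring may explain part of the difference.

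**A reader might also infer that episodes provoked by the intervention would go unseen.** Nothing in the article indicates that the intervention provokes episodes, and QIDS-SR and ASRM at T2 give some symptom information from both arms for that period. Only the relapse interview is blind to it.

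**Conclusion.** The gap is real and follows from the article's own dates: no relapse information for months 0 to 3, which is a quarter of follow-up and includes the whole intervention. The nine-month window matches neither randomisation nor the stated post-intervention scope, and Study procedure and Relapse need to be reconciled. As written, the Kaplan-Meier and relative-risk analyses would count patients who relapse only in the gap as relapse-free, so they do not compare the randomised groups over 12 months.

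The size and direction of any resulting bias are not known. The 27% to 34% share of first relapses rests on an assumed common 12-month risk of 20% to 60% and a constant hazard. The 5-week figure rests on treatment starting at baseline, as Study design says.

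This should be fixed, but it is not critical to the trial: relapse is not the primary outcome, and the sample size and primary analysis do not depend on it.

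**What to change.** Set the Life Chart look-back to the full 12 months from T0/randomisation in both arms, and start Kaplan-Meier time at randomisation. Change the nine-month wording in Study procedure and the post-intervention wording in Relapse to match, and state the time origin in Statistical analyses. An analysis restricted to the period after the intervention can be kept as supplementary, with the same calendar start in both arms.

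The cost is small. The interview guideline has yet to be prepared and no extra visit is needed. The recall period lengthens from 9 to 12 months, with somewhat more recall error, and the call, planned at about 30 minutes, would run slightly longer.
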